### Drug administration

Following initial consent and screening on day zero, varenicline (or matched placebo) will be prescribed for one week, to be taken as 0.5 mg once daily for days one to three, as 0.5 mg twice daily for days four to six, and as 0.5 mg once daily for day seven, consistent with the standard dosing regimen for smoking cessation. Participants will attend their second session on day seven (their last drug intake day) and will be advised to take the drug in the morning prior to their study session.

Study medication will be administered to the participant by a designated medical doctor following screening on day zero. This method of prescription is comparable with the administration of varenicline in general practice. Participants will be required to complete a daily diary detailing the time at which drugs are taken and any side effects. They will be asked to bring the diary and drug bottle to their second session.

### Outcome measures

Primary outcome measures are changes in cognitive bias as measured by the visual dot-probe task, and neural responses to smoking-related cues. Secondary outcome measures will be cognitive bias as measured by a transfer task (modified Stroop test) and subjective mood and cigarette craving as measured by the Questionnaire of Smoking Urges (QSU) and the Minnesota Nicotine Withdrawal Scale (MNWS). Measures and materials.

#### Materials

Stimuli for the CBM and fMRI cue exposure task comprise 32 full-colour smoking-related pictures and 32 neutral pictures. Smoking-related cues consist of full-colour pictures of people smoking. Control cues consist of full-colour pictures of people engaged in everyday activities (such as talking on the telephone or writing). Equal numbers of females and males are represented in each category. The set of cues pictures is the same as those used in previous imaging studies [26]. For the cognitive bias modification task, an additional four picture pairs, unrelated to smoking, are used in practice and buffer trials.

#### Cognitive bias modification

For the CBM, participants will be randomized to complete a version of the visual probe task designed to induce a biased cognitive response away from (avoid: n = 24), or towards (attend: n = 24) smoking-related cues, or a control condition (control: n = 24) designed not to modify cognitive bias. Each task version comprises a total of 768 trials. On each trial, following a 500 ms duration fixation cross, a picture pair is presented on a computer screen for 500 ms. When this picture pair disappears, a probe is presented in either of the two screen locations previously occupied by a picture. This probe is either a small circle or square. Participants are required to discriminate between the identity of each probe by pressing the arrow keys on the keyboard as appropriate, and the response latency is measured. The majority (n = 512) of trials are training trials, presented in four blocks, and the remainder (n = 256) of trials are test trials. Half of the test trials (n = 128) are presented prior to the training trials, and half (n = 128) after the training trials, in order to assess the effect of the training trials on cognitive bias. In the test trials, the probe appears with equal frequency in the vicinity of both the smoking-related or neutral pictures. In the training trials, the probe appears in the vicinity of the neutral picture on 75% of trials in the avoid condition, or appears in the vicinity of the smoking-related picture on 75% of trials in the attend condition, or appears with equal frequency in the vicinity of neutral and smoking-related pictures in the control condition. The inter-trial interval is jittered between 750 ms and 1,250 ms in order to reduce the monotony of the task. The sequence of events will be controlled using EPrime version 2 software (Psychology Software Tools Inc., Pittsburgh, Pennsylvania, United States), and the total task time is approximately 50 minutes.

#### Cognitive bias test (modified Stroop)

A pictorial version of the modified Stroop task will be used in favor of the more traditional lexical version, due to recent evidence of greater internal reliability of pictorial versions of the task [27]. The task begins with 16 practice trials followed by two experimental blocks, each comprising eight buffer and 96 experimental trials (208 trials in total). For each trial a picture is presented (smoking-related or neutral) centrally on screen. The picture is surrounded by a colored border and the participant is required to identify the colour of the border (red, blue, yellow, or green) using colour-marked keys on the keyboard (d, f, j, and k).

#### Questionnaires

The questionnaire measures will include the Eysenck Personality Questionnaire - Revised (EPQ-R) [28], the Questionnaire of Smoking Urges - Brief (QSU-Brief) [29], the Minnesota Nicotine Withdrawal Scale (MNWS) [30], and visual analogue scales (VAS) of mood and cigarette craving. These data will be used to examine group differences at baseline and to assess any changes in mood or craving across the course of the study.

#### functional Magnetic Resonance Imaging(fMRI) acquisition

An anatomical and an fMRI scan will be performed on the test day session (day seven). During the fMRI cue exposure procedure, smoking-related and control cues will be presented in a boxcar design with four blocks per category (Figure 2). Participants are required to make a button press on each stimulus presentation to identify they have seen the image (this does not terminate viewing time). Each block will be 40 seconds in length, during which time eight cues will be presented. Before and after each block, a crosshair will be presented for five seconds. Participants will then be asked to rate their craving level on an eight-point scale (‘none at all’ to ‘extreme’). The scale will be presented for 10 seconds followed by presentation of a crosshair for another 10 seconds. Thus, the total between-block interval is 25 seconds. The sequence of events will be controlled using EPrime version 2 software (Psychology Software Tools Inc., Pittsburgh, Pennsylvania, United States), and the total task time is approximately 10 minutes. The total MRI protocol will last approximately 15 minutes.

**Figure 2 Fig2:**

**Timeline of cue-exposure task conducted during the functional Magnetic Resonance Imaging.**

### Data collection procedures

Day zero will be for screening and baseline assessments. After informed consent has been obtained, the screening procedure will be conducted. Expired breath alcohol and carbon monoxide readings will be taken and height, weight, blood pressure, and heart rate measured. A urine screen will be performed to test for recent drug use (all) and pregnancy (females). A medical doctor will perform a general physical and psychiatric health assessment and prescribe the study medication if appropriate. Post-screening, participants will complete a baseline assessment of cognitive bias (modified Stroop) and questionnaires assessing personality, cigarette craving, and mood. They will also complete a practice version of the task that will be used during the fMRI scan at the second study visit.

Participants will be sent away with the study medication, medication packaging information, and a drug diary (which they will be required to complete and return at the next visit). The second session (test day) will be scheduled for approximately one week later. This session will fall on day seven of their drug regimen.

On the test day, participants will complete the modified Stroop task followed by a short visual dot-probe task that measures baseline cognitive bias. They will then be randomized to one of three conditions: 1) an experimental condition designed to induce cognitive bias towards smoking-related cues (attend), 2) an experimental condition designed to induce cognitive bias away from smoking-related cues (avoid), or 3) a control condition designed to induce no change in cognitive bias (control). The test version of the dot-probe task will be run again immediately post-CBM in order to assess changes in cognitive bias.

Following this, participants will be taken to the scanning suite. All participants will complete a four-minute anatomical scan followed by the cue-exposure test during a 15-minute fMRI scan. After scanning, participants will complete the modified Stroop task and questionnaire state measures (QSU and visual analogue scales). At the end of the test session, participants will be offered smoking cessation literature, debriefed, and reimbursed (£70).

### Statistical plan

#### functional Magnetic Resonance Imaging analysis

Analyses will focus on evaluating neural activation during viewing of smoking-related and control cues in the three experimental groups. Pre-processing will be conducted using statistical parametric mapping software (Statistical Parametric Mapping 5; Wellcome Department of Imaging Neuroscience, London, United Kingdom) to remove noise and artefacts. The first four volumes of each run will be discarded to allow for T1 stabilization. All functional images will be corrected for acquisition timing and head motion using rigid-body rotation and translation. Each participant’s data will then be warped into a standard stereotaxic space (Montreal Neurological Institute) with an isotropic 2 mm voxel size and smoothed with an 8 mm full width at half measure (FWHM) Gaussian filter.

Each participant’s fMRI data will then be entered into a first-level voxel-by-voxel analysis using the general linear model. Each cue block (smoke or control) will be modelled as a boxcar function convolved with a canonical hemodynamic response function that begins at the onset of the first cue in the block and ends at the end of the block (60-second duration). A high-pass filter will be applied to remove slow signal drift. A smoking-related cue greater than control cue contrast image will then be created and inputted into a random effects analysis. A two (varenicline and placebo) × three (attend, avoid, and control) mixed-model analysis of variance (ANOVA)will be used to examine smoking cue reactivity (smoking greater than control) between each group. Voxel-wise analysis will be conducted within an Region of Interest (ROI) mask. The mask will be created from anatomical regions identified in a meta-analysis of cue reactivity [31]: nucleus accumbens, caudate, putamen, temporal gyrus, anterior cingulate gyrus, amygdala, insula, posterior cingulate cortex, inferior frontal gyrus, and angular gyrus. Each bilateral region will be selected using the WFU PickAtlas tool [32] and combined to create the mask. Resulting activations will be considered significant at an alpha level of 0.001 (uncorrected) with a minimum cluster extent threshold of 20 contiguous voxels. *Post hoc* analyses of parameter estimates will be used to evaluate the nature of significant effects. Smoking cue greater than control cue contrast images for each participant will also be input into random effect regression analyses examining relations between post-training cognitive bias scores and neural cue reactivity.

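### The first-level fMRI model gives the cue block a 60-second duration, while the acquisition section sets the same block at 40 seconds; the two must be reconciled before contrast images are made

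*Protocol article*

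**What the plan says.** All places are in the protocol article.

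- **fMRI acquisition section.** On the block itself: "Each block will be 40 seconds in length, during which time eight cues will be presented". A 5 s crosshair stands on either side of the block, and the craving rating comes after it: "The scale will be presented for 10 seconds followed by presentation of a crosshair for another 10 seconds". The section sums the gap itself: "Thus, the total between-block interval is 25 seconds". The design has eight blocks: "smoking-related and control cues will be presented in a boxcar design with four blocks per category".
- **fMRI analysis section.** Each cue block, smoking or control, is a boxcar convolved with a canonical haemodynamic response. It "begins at the onset of the first cue in the block and ends at the end of the block (60-second duration"). High-pass filtering is also planned; its cut-off is not given. The smoking-greater-than-control image from this model goes into the 2 × 3 ANOVA (drug by CBM group) and into the regressions of neural cue reactivity on post-training bias scores.
- **Outcome measures section.** Neural response to smoking cues is one of the two primary outcomes.

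**The concern.** The two sections give different durations for the same event, and the one in the analysis section is the number an analyst would code. Nothing in the article defines a block as including the rating; the acquisition section puts the rating in the gap between blocks.

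If 60 s is coded and 40 s is presented, the regressor continues through fixation and the craving rating. Two things follow for the contrast. The cue effect is diluted, because a third of the modelled period contains no cues. Also, any activity during the rating that differs after smoking and control blocks is counted as cue reactivity. Such a difference is plausible, since participants are rating craving just after seeing smoking or neutral pictures. That matters for a study whose Background asks whether CBM lowers the emotional response to cues or raises cognitive control in their presence.

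**Working it through.** **1. Timeline from first-cue onset (acquisition section).**

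| Seconds | Event |
|---|---|
| 0–40 | eight cues |
| 40–45 | crosshair |
| 45–55 | craving rating |
| 55–65 | crosshair |

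The stated interval reproduces: 5 + 10 + 10 = 25 s. If the 5 s crosshair before the next block is counted separately, it is 30 s.

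**2. Attempts to reach 60 s.**

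- Block plus the two 5 s crosshairs: 40 + 5 + 5 = 50 s.
- Block plus the whole interval: 40 + 25 = 65 s.
- Pre-block crosshair through rating: 5 + 40 + 5 + 10 = 60 s, but this starts 5 s before the first cue, against the stated onset.
- First cue plus 60 s: 40 + 5 + 10 + 5 = 60 s, but this stops halfway through the last crosshair, which is not the end of any block.

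The stated 60 s is not reproduced under the stated start and end.

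**3. Can other figures settle which length is right?**

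- Cue count: 4 blocks × 8 cues = 32 per category, matching the 32 pictures of each kind in the Materials section. This supports eight cues per block but not a particular block length.
- Task time, stated as "the total task time is approximately 10 minutes". Shortest case: 8 blocks and 7 gaps of 25 s. Longest case: 8 blocks, 8 gaps of 30 s and a 5 s lead-in.
  - 40 s blocks: (320 + 175)/60 = 8.3 min to (320 + 240 + 5)/60 = 9.4 min.
  - 60 s blocks: (480 + 175)/60 = 10.9 min to (480 + 240 + 5)/60 = 12.1 min.

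  The stated time lies between the two ranges and does not decide.

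**4. Overlap if 60 s is coded and 40 s is presented.** 60 − 40 = 20 s of non-cue time, and 20/60 = 33%. It is made up of 5 s crosshair, the full 10 s rating and 5 s of the next crosshair.

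**5. Illustration of the effect on the contrast.** Assumptions, none of them from the article: double-gamma response, alternating blocks, ordinary least squares (white noise), no high-pass filter, no separate rating regressor. The fitted model is signal = b₁·smoking + b₂·control + constant, and the contrast is b₁ − b₂.

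| True signal | Model | 25 s gap | 30 s gap |
|---|---|---|---|
| Cue difference of 1, no rating response | 60 s | 0.66 | 0.66 |
| Rating-only smoking-minus-control difference of 1 | 60 s | 0.18 | 0.18 |
| Rating-only smoking-minus-control difference of 1 | 40 s | −0.01 | −0.02 |
| Rating response equal after both cue types | 60 s | 0.00 | 0.00 |

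The unfiltered 60 s values hardly change with block order. They are sensitive in two other respects. With high-pass cut-offs of 128–300 s and different block orders and gaps, the recovered cue contrast ran from 0.18 to 0.68, and the leakage under a 40 s model no longer stayed near zero. With separate rating regressors added to the unfiltered 60 s model, it was about 0.85.

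**The case against.** The best reply is that the analysis sentence states its own rule correctly. The boxcar runs from the first cue to the end of the block, which is 40 s on the acquisition section's timings, so the 60 s in brackets may be a slip that was never coded. It is also possible that 60 s blocks are presented and the acquisition text is wrong, in which case the boxcar would not run past the cues. The timeline figure, which might settle this, is not shown. This reply stands as far as it goes: it makes the harm conditional. It does not remove the contradiction, because 60 s is the only duration the analysis text gives.

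A reader might infer more than the documents support in four respects:

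- **That the contrast does mix viewing with rating.** This happens only if 60 s is coded while 40 s is presented, and the article does not establish that.
- **That the rating period is left out of the model.** The article describes the cue regressors and does not say they are the only ones. A condensed article commonly leaves further regressors to the full plan, so its silence is no defect.
- **That a group difference could no longer be attributed to cue viewing.** Rating activity common to both cue types largely cancels. To bias a comparison of arms, the cue-specific part would itself have to differ between arms, which is possible but not shown.
- **That every group comparison is affected.** The dot-probe, Stroop and questionnaire analyses do not use this contrast.

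Nor does the 0.66 translate into lost power. A scaling shared by all participants also rescales the between-subject variation in signal, so it does not carry over one-for-one to the random-effects test.

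**Conclusion.** The point holds as a contradiction in a number the analysis relies on: the same cue block is 40 s in one section and 60 s in another, and no stated timing reconciles them. It bears on the primary neural outcome, through the 2 × 3 fMRI ANOVA and the bias–reactivity regressions.

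The firm figure is conditional: if 60 s is coded over 40 s blocks, 20 of 60 modelled seconds (33%) are not cue viewing and include the entire craving rating. The contrast is then diluted and open to rating activity that differs by cue type. The values of about 0.66 and 0.18 illustrate direction and rough size only; they rest on the assumptions listed in the working, including the absence of the high-pass filter that the article says will be used. No group-level power loss has been computed.

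**What to change.** Before any contrast image is produced:

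1. Check the presented block length against the E-Prime task file and the logged onsets.
2. State that one duration in both the acquisition and the analysis sections.
3. Set the boxcar to the presented cue duration (40 s if the acquisition section is right), so that it ends before the craving rating.

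A separate regressor for the 10 s rating is an optional addition and is not needed to resolve the contradiction.

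The cost is one number in the text and, if 60 s has been coded, one number in the first-level script. No new data are needed. The Trial status section reports 55 participants enrolled by March 2014 and data collection projected to finish in June 2014, so on that timetable the check could precede the final analysis.

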### Study objectives and hypotheses

The primary objective is to investigate the neural effects of CBM in response to smoking-related cues in current daily smokers. A secondary objective is to examine the effects of varenicline treatment on neural responses to smoking cues. We will also explore whether there is any pattern in the data to suggest that the effects of CBM are modified by concurrent treatment with varenicline. The CBM methods we will use are delivered via computer, and can therefore in principle be delivered remotely and repeatedly at low cost, for example via the internet or smartphones, as an adjunctive treatment to varenicline pharmacotherapy. To investigate whether CBM and varenicline effects generalize to other measures of cognitive bias, participants will also complete a modified pictorial Stroop task before and after CBM and varenicline.

We hypothesize that: 1) CBM designed to induce cognitive bias towards smoking-relates cues will lead to an increase in cognitive bias and neural response to smoking-related cues in brain regions previously implicated in cue reactivity in cigarette smokers; 2) CBM designed to induce cognitive bias away from smoking-relates cues will lead to a decrease in cognitive bias and neural response to smoking-related cues in brain regions previously implicated in cue reactivity in cigarette smokers; and 3) varenicline treatment will lead to a reduction in the neural response to smoking-related cues.

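### The group fMRI analysis tests only smoking minus control, and CBM also trains the control pictures by arm, so a CBM effect shows a relative change and does not by itself show a change in response to smoking cues

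*Protocol article*

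**What the plan says.** All places are in the protocol article.

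- **Functional Magnetic Resonance Imaging analysis.** The first-level model separates the cue types: "Each cue block (smoke or control) will be modelled as a boxcar function convolved with a canonical hemodynamic response function". Only their difference goes further: "A smoking-related cue greater than control cue contrast image will then be created and inputted into a random effects analysis". The drug-by-CBM ANOVA "will be used to examine smoking cue reactivity (smoking greater than control) between each group". The regression on bias scores has the same input: "Smoking cue greater than control cue contrast images for each participant will also be input into random effect regression analyses". The only follow-up is that post hoc "analyses of parameter estimates will be used to evaluate the nature of significant effects".
- **Materials.** One picture set serves training and scan: "Stimuli for the CBM and fMRI cue exposure task comprise 32 full-colour smoking-related pictures and 32 neutral pictures".
- **Cognitive bias modification.** During training, "the probe appears in the vicinity of the neutral picture on 75% of trials in the avoid condition". In the attend arm the 75% is at the smoking picture, and in the control arm the split is even.
- **Study objectives and hypotheses.** Hypothesis 2 is that avoid training "will lead to a decrease in cognitive bias and neural response to smoking-related cues". Hypothesis 1 predicts an increase after attend training.
- **Trial design.** Cue type is named as a within-subjects factor for the scanner task. The fMRI analysis section absorbs it into the contrast.

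**The concern.** Subtracting the control-cue response isolates the smoking-cue response only if the randomised treatment leaves the control-cue response alone. Randomisation makes the arms comparable before training. It does not hold the reference fixed when the training acts on the reference. Here the neutral pictures receive the mirror image of the training given to the smoking pictures.

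A lower contrast in the avoid arm could therefore mean a weaker response to smoking pictures, a stronger response to everyday scenes, or some of each. The Background section says the data should show whether CBM dampens emotional response to drug cues or strengthens control in their presence. For a mechanism study, reporting a reduced smoking-cue response when only the reference moved would be a wrong conclusion about the primary objective.

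**Working it through.** **1. Trial counts (Cognitive bias modification).** The plan's total reproduces: 512 training + 256 test = 768 trials.

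Probes at the neutral picture, training trials:
- avoid: 0.75 × 512 = 384
- control: 0.50 × 512 = 256
- attend: 0.25 × 512 = 128

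Probes at the smoking picture are 128, 256 and 384 in the same order, so the two categories are manipulated by equal amounts in opposite directions.

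The 256 test trials are split evenly and add 128 neutral-picture probes in every arm. The totals become 512, 384 and 256. If the 32 pairs are used equally (an assumption), each neutral picture has 16, 12 and 8 probes before the scan. The ratio of avoid to attend is 3 on training trials and 2 on all trials.

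**2. What the contrast identifies.** For any two arms,

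arm difference in contrast = shift(smoking) − shift(control).

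Three different truths for attend / control / avoid:

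| Truth | Smoking response | Control-picture response | Contrast |
|---|---|---|---|
| Only smoking moves | +0.5, 0, −0.5 | 0, 0, 0 | +0.5, 0, −0.5 |
| Only control moves | 0, 0, 0 | −0.5, 0, +0.5 | +0.5, 0, −0.5 |
| Half each | +0.25, 0, −0.25 | −0.25, 0, +0.25 | +0.5, 0, −0.5 |

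The contrast is the same in each row, so neither the ANOVA nor the regression can distinguish them.

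**3. Illustration.** Assumed: 24 per arm, a linear trend of 0.5 per arm step, SD 0.707 per condition with independent errors (so SD 1 for the difference), one region, two-sided alpha 0.05. The arm scores +1, 0, −1 have sum of squares 48, so the trend statistic for the contrast is about 0.5 × √48 / 1 = 3.46 in every row, which is power of about 93%. Simulation agrees:

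| Truth | Contrast rejects | Smoking alone rejects | Control pictures alone reject |
|---|---|---|---|
| Only smoking moves | 92% | about 100% | 5% |
| Only control moves | 94% | 4% | about 100% |
| Half each | 93% | 68% | 68% |

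Differences within the contrast column are simulation noise. The effect size is invented; the table shows only that separate estimates tell the rows apart and the contrast does not.

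**4. Can the crosshair serve as baseline as modelled?** The acquisition section gives 40-second blocks, then 5 s crosshair, 10 s craving rating and 10 s crosshair. That reproduces its interval of 5 + 10 + 10 = 25 s and gives a cycle of 65 s. The analysis section models each block as 60 s. From block onset this takes in 40 s of cues, 5 s of crosshair, the 10 s rating and 5 s of the next crosshair. It leaves 65 − 60 = 5 s of baseline per cycle and mixes rating activity into the cue estimate. With assumed 2-second sampling and white noise, over two block orders and with or without a 128-second filter, the standard error of smoking against baseline under the 60-second model is about 1.6 to 1.8 times that under a 40-second model, and 1.2 to 2.0 times that of the smoking-minus-control difference. With 40-second blocks and the rating modelled separately, 65 − 40 − 10 = 15 s of crosshair remains per cycle.

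**The case against.** **The plan already has a step for this.** Smoking and control blocks are modelled separately, so estimates for each exist, and asking which one drives an effect falls naturally under a post hoc look at its nature. This largely stands. A reader might infer that the study cannot attribute a CBM effect to smoking cues at all. The documents do not support that: the limit lies in the planned test, not in the data collected. But the text does not say that the post hoc estimates are taken per cue type, and the step is triggered only by a significant contrast.

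**Cue reactivity is relative by definition.** The analysis section defines it as smoking greater than control, the bias score is also a difference, and CBM trains a preference within pairs. This is a good reason to keep the contrast. It does not license the wording of hypotheses 1 and 2, which concern the response to smoking-related cues.

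**The mechanism is conjecture.** A reader might infer that training does change the neural response to neutral pictures. Nothing in the article shows this. In the scanner the pictures appear in single-category blocks with no probe, and every image gets a button press. The objection stands: the shift is possible, and the plan neither tests it nor rules it out.

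**The dose difference is smaller than it looks.** Correct. The threefold range holds for training trials only; over all trials it is twofold.

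**A simple direction rule would not help.** Also correct. If the smoking response has not moved, its estimate still points the predicted way about half the time in a single attend-avoid comparison.

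**Conclusion.** The point holds as a limit on interpretation. The reference condition is itself trained by arm, so a CBM effect on smoking minus control demonstrates a change in relative response. By itself it does not demonstrate the change in response to smoking cues stated in hypotheses 1 and 2. The share of such an effect that comes from neutral pictures is not known from the documents. It would be half if training moved both categories equally and oppositely, and none if neutral responses did not move.

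This rests on the shared picture set and on the post hoc step being as unspecific as it is written. It does not invalidate the contrast or the data. It does not reach hypothesis 3 in this way, because varenicline does not train the control pictures. The plan should be changed, since the remedy is cheap and bears on the primary objective.

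**What to change.** In the fMRI analysis section:

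1. Keep smoking greater than control as the planned test.
2. Reconcile the modelled block duration (60 seconds) with the acquisition section (40 seconds), and model the craving-rating period separately, so that the crosshair can serve as baseline.
3. Specify that smoking-versus-crosshair and control-versus-crosshair estimates are taken from the first-level model, averaged over the anatomical regions of the mask, and compared between CBM arms with effect estimates and confidence intervals, whether or not the contrast is significant.
4. State that a CBM effect is attributed to smoking cues only as far as the smoking-cue estimate and its interval support it. Otherwise the conclusion is limited to a change in relative response.

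The cost is a corrected first-level model and two further contrasts per participant. It needs no new scanning or pictures, which matters because the Trial status section reports 55 of the planned 72 participants already enrolled. The downside is that single-condition estimates may be less precise than the difference. They should therefore guide interpretation and not act as a second significance test.

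### The significance rule for the primary neural outcome (uncorrected p<0.001, 20 voxels, ten bilateral regions) does not control false positives

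*Protocol article*

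**What the plan says.** Under Outcome measures, the Protocol article states: "Primary outcome measures are changes in cognitive bias as measured by the visual dot-probe task, and neural responses to smoking-related cues". Under Study objectives and hypotheses, the neural effect of CBM is the main aim: "The primary objective is to investigate the neural effects of CBM in response to smoking-related cues in current daily smokers". The varenicline effect is a secondary objective, and the CBM-by-drug interaction is to be explored.

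The section on fMRI analysis fixes how this outcome is tested:

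- **Images:** prepared "with an isotropic 2 mm voxel size and smoothed with an 8 mm full width at half measure (FWHM) Gaussian filter".
- **Model:** "A two (varenicline and placebo) × three (attend, avoid, and control) mixed-model analysis of variance (ANOVA)will be used to examine smoking cue reactivity". This yields three effects: drug, CBM and their interaction.
- **Search volume:** voxel-wise within a mask made of "nucleus accumbens, caudate, putamen, temporal gyrus, anterior cingulate gyrus, amygdala, insula, posterior cingulate cortex, inferior frontal gyrus, and angular gyrus". All ten areas, taken on both sides of the brain, are merged into a single search volume.
- **Decision rule:** "Resulting activations will be considered significant at an alpha level of 0.001 (uncorrected) with a minimum cluster extent threshold of 20 contiguous voxels".

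The article mentions no family-wise, false-discovery-rate or small-volume correction. It does not derive the 20-voxel extent or divide error between the three effects. A further voxel-wise regression on post-training bias scores is planned without a threshold of its own.

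**The concern.** A threshold of 0.001 applies to one voxel. Searching thousands of voxels and accepting any group of 20 that passes gives a map-wise error rate that depends on the number of voxels searched and on how smooth the images are. The rule takes account of neither.

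This is not a detail left for an analysis plan to fill in. The article labels the rule uncorrected, so a later corrected rule would contradict it.

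The rule bears on the neural part of hypotheses 1 and 2 and on the whole of hypothesis 3, which concerns neural response only. It also decides which effects go forward to the post hoc look at parameter estimates. If it passes noise often, a positive neural finding cannot be read as confirmation.

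**Working it through.** **No figure to reproduce.** The article states no map-wise error rate for the neural outcome. The natural benchmark is the 0.05 alpha used under Sample size determination.

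**Inputs from the article.** Voxel edge 2 mm, so voxel volume is 2³ = 8 mm³. Applied filter 8 mm FWHM. Voxel threshold p<0.001. Extent 20 voxels. N = 72 in six cells, so residual degrees of freedom are 72 − 6 = 66, giving F(1,66) for drug and F(2,66) for CBM and for the interaction.

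**Assumed, because the article does not give them.**

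- Mask size: 4,320 to 39,200 voxels.
- Mask shape: 20 separate blocks, or one solid block for the largest mask.
- Effective smoothness: 8 to 12 mm. The filter adds to the smoothness already in the images, roughly √(8² + s²) for intrinsic smoothness s. So 8 mm is a floor, and s = 6 mm gives √(64 + 36) = 10 mm.

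**Step 1: the extent rule in context.** 20 × 8 = 160 mm³. One 8 mm resolution element is 8³ = 512 mm³, or 64 voxels, and 160/512 = 0.31. The extent is therefore small relative to the smoothness, although this ratio is not itself an error rate.

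**Step 2: voxels expected by chance.** 0.001 × mask size: 10 voxels for a mask of 10,000, 20 for 20,000, 40 for 40,000. Because of smoothing these come in clumps.

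**Step 3: chance of at least one cluster of 20 or more voxels with no true effect.** Smooth Gaussian null fields for 72 participants, exact F maps, 18-neighbour clusters; 1,500, 1,000 and 800 runs at 8, 10 and 12 mm.

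| Mask, voxels (cm³) | Smoothness | Drug | CBM | Interaction | Any of three |
|---|---|---|---|---|---|
| 4,320 (35) | 8 mm | 2.3% | 1.5% | 1.6% | 5.3% |
| 4,320 (35) | 12 mm | 5.2% | 3.9% | 5.5% | 14.1% |
| 10,240 (82) | 8 mm | 6.6% | 5.4% | 5.8% | 16.9% |
| 10,240 (82) | 10 mm | 11.5% | 9.3% | 9.6% | 27.2% |
| 10,240 (82) | 12 mm | 14.9% | 13.0% | 15.0% | 36.5% |
| 20,000 (160) | 8 mm | 13.3% | 11.4% | 10.7% | 30.7% |
| 20,000 (160) | 10 mm | 23.0% | 20.9% | 19.1% | 51.0% |
| 20,000 (160) | 12 mm | 25.5% | 22.1% | 26.9% | 57.5% |
| 34,560 (276) | 8 mm | 23.9% | 20.4% | 20.1% | 51.7% |
| 34,560 (276) | 12 mm | 40.5% | 41.0% | 41.4% | 79.9% |
| 39,200 (314), solid | 8 mm | 30.7% | 27.6% | 27.3% | 63.9% |
| 39,200 (314), solid | 12 mm | 46.4% | 46.9% | 47.9% | 83.4% |

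The simulation error is modest: √(0.133 × 0.867 / 1,500) ≈ 0.9 percentage points for the drug effect at 20,000 voxels and 8 mm.

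A separate simulation with normal and chi-square approximations, over masks of 117 to 352 cm³ and 8 to 12 mm, gave about 26-88% for any of the three effects.

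**Step 4: leaving out the exploratory interaction.** Treating drug and CBM as independent at 20,000 voxels:

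- 8 mm: 1 − 0.867 × 0.886 = 23%
- 10 mm: 1 − 0.770 × 0.791 = 39%
- 12 mm: 1 − 0.745 × 0.779 = 42%

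**Step 5: extent that would hold 5%.** These are the approximate 95th percentiles of the largest null cluster over 8 to 12 mm.

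| Mask, voxels | One effect | Three effects jointly |
|---|---|---|
| about 10,000 | 20-36 | 28-55 |
| 20,000 | 26-50 | 35-73 |
| 35,000-39,000 | 31-80 | 42-112 |

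Twenty voxels is at or below the bottom of every range.

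**The case against.** **The size depends on a mask volume the article does not give.** This stands. The temporal gyrus is not specified further, and for a mask of about 10,000 voxels at exactly 8 mm the rate per effect is 5-7%, close to nominal. Even there the three-effect rate is 17%, and 8 mm is the least smoothness the images can have.

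**Pooling three effects overstates the problem.** This stands in part. CBM is primary, varenicline secondary and the interaction exploratory. The per-effect columns and Step 4 answer it: CBM alone is at 11-22% for 20,000 voxels, and CBM with drug at 23-42%.

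**The extent rule removes most noise.** This is true. At 20,000 voxels and 8 mm, about 97-99% of null maps per effect contain some voxel past the threshold; with the extent rule it is 11-13%. In a one-sided null map at 8 mm the median noise cluster was 5 voxels and about 11% reached 20. The comparison with a 512 mm³ smoothing cube should therefore not be read as saying that a typical noise peak passes. The rule reduces false positives, but not to a known level.

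**A false cluster is not yet a supported hypothesis.** This is fair for hypotheses 1 and 2, which are directional and also require a change in cognitive bias, tested separately. It protects hypothesis 3 less, since that rests on the neural response alone.

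**This is a laboratory study that informs later work, with an openly labelled threshold and a pre-defined mask.** Openness and a restricted mask help, but the article still names this a primary outcome and uses the rule to call results significant.

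**Conclusion.** The concern holds, and the rule should be changed before the neural outcome is analysed. The stated rule does not control the map-wise error rate.

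For masks of 20,000 to 39,200 voxels and smoothness of 8 to 12 mm, the chance of at least one false cluster is about 11-48% per effect and 31-83% over the three ANOVA effects. It is near 5% per effect only for masks of about 10,000 voxels or fewer at 8 mm, and over three effects only at about 4,300 voxels. A mask with both sides of the temporal gyrus, inferior frontal gyrus, insula and cingulate areas is unlikely to be that small.

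The figures assume stationary Gaussian noise and the stated mask sizes and shapes. The voxel-wise regression and the dot-probe primary outcome would add to the error and are not counted. The direction of the finding does not depend on the sample size. The exact size does depend on the real mask and the estimated smoothness.

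**What to change.** Replace the decision rule by one of two options:

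1. Keep p<0.001 as the cluster-forming threshold and declare significance only at family-wise-error-corrected p<0.05, at cluster or peak level, with small-volume correction for the pre-defined mask.
2. Make the primary neural test the mean smoking-minus-control contrast over each pre-defined anatomical region, with Holm correction over the regions.

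In either case, state the mask volume and exact region definitions, and apply the same rule to the regression. State also whether the 5% is held for each effect or jointly. The article's own ranking (CBM primary, drug secondary, interaction exploratory) is a natural basis for that choice. Report uncorrected maps as descriptive only.

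The change needs plan wording and a standard option in the software already named. Recruitment, scanning and sample size are unaffected. Trial status reports 55 of 72 enrolled in March 2014 with data collection to end in June 2014, so at that point the rule could still be amended before collection closed. The price is sensitivity: fewer voxels will reach significance. How much power is lost cannot be calculated, because the article says that the neural effects had not been evaluated before.
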